### Participants and Recruitment

We will recruit participants in the Rehabilitation Hospital affiliated to Fujian University of Traditional Chinese Medicine. All participants need to meet the LDH diagnostic criteria in the guidelines for clinical diagnosis and treatment (Orthopedic Bundle Separation) [20]. In addition, we will recruit potential patients through posters and internet platforms. Clinical trial communicators will fully explain the trial to patients before the trial begins to ensure that all the patients participate voluntarily and sign an informed consent form.

### Inclusion Criteria

The inclusion criteria for the participants are as follows: (1) right-handed; (2) age between 18 and 60 years; (3) computed tomography or magnetic resonance imaging examination show L4-L5 or L5-S1 disc herniation; (4) the main manifestation is nerve root pain, and the imaging is consistent with the nerve localization; (5) the neuropathic pain rating scale (Douleur Neuropathique 4 questions) score is ≥4; (6) patients who did not take painkillers or nutritional neurodrugs for nearly 1 month and did not receive systematic treatment; and (7) patients who voluntarily want to participate in clinical trials and sign informed consent forms.

### Exclusion Criteria

The exclusion criteria are as follows: (1) patients with progressive neurological deficit or cauda equina syndrome; (2) patients with LDH combined with other major lumbar diseases such as tumor, tuberculosis, and severe osteoporosis; (3) patients with trauma, acute lumbar injury caused by surgery pain, and lower limb nerve injury; (4) patients with any other condition causing lower limb neuropathy (diabetes or neurological diseases); (5) patients with cardiovascular, pulmonary, renal, hematopoietic system, and other major diseases; (6) patients with mental health issues; (7) pregnant or lactating women; and (8) patients with contraindications for fMRI.

### Dropout Criteria

Participants who were unable to complete the trial for the following reasons will be considered to have dropped out: (1) patients are not treated by the regulations, and the curative effect cannot be judged; (2) incomplete data that affect the judgment of efficacy or safety; or (3) accidents occur in the course of treatment and participants are unable to adhere to treatment.

### Comprehensive Suspension Criteria

The comprehensive suspension criteria are as follows: (1) participants in the study have serious adverse effects due to a poor treatment plan, (2) participants experience severe complications or disease deterioration during the study period, and (3) if the test termination conditions are met after the doctor follows the standard operating procedure treatment, they shall be terminated immediately.

### Randomization

An independent technician will use the SPSS statistical software (version 26.0; IBM Corp) to generate random sequence numbers, and participants will be randomly divided into the Tuina intervention group or the traction with TENS intervention group in 1:1 ratio. Random sequence numbers will be sealed in opaque envelopes. The envelopes will be opened in a numerical order to determine the allocation for the participants.

### Blinding

In this study, blindness will be implemented for outcome evaluators and data statisticians. Due to the particularity of the treatment method in this trial, the therapists and patients will not be blinded for their grouping. This blinded process will continue until the end of the trial data analysis.

### Interventions

Participants will receive treatment once a day for 14 days. Tuina treatment will be performed by a professionally trained Tuina therapist, and a senior attending physician will perform TENS and traction. Before the trial, both operators should pass the relevant clinical tests to ensure the operation’s consistency. Other related treatments such as medicines, acupuncture, and physiotherapy will not be allowed during the treatment period.

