#### Quality Control of the Research Participants

Before the study begins, we will provide each participant with details about the operability and precautions of the intervention method, prohibit other treatment methods during the intervention, and provide free health counseling throughout the study. With the informed consent of the participants, the corresponding test contents can be included and conducted voluntarily. If the pain fails to be relieved during the intervention, the project team must be informed in time and relevant drugs must be given if necessary; if the symptoms cannot be relieved, comprehensive treatment should be given immediately. If there is an accident or adverse event during a treatment event, the record form should be filled accurately, providing details such as the adverse event type, occurrence time, severity, duration, measures taken, and other reports.

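### The ban on other treatment conflicts with the instruction to give drugs for unrelieved pain, and the dropout rule could make data loss depend on treatment failure

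*Protocol article*

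**What the plan says.** Four places in the protocol article bear on this point.

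- **Interventions:** "Other related treatments such as medicines, acupuncture, and physiotherapy will not be allowed during the treatment period". No exception or cross-reference is given.
- **Quality Control of the Research Participants:** the team will "prohibit other treatment methods during the intervention". The same paragraph then sets a trigger: "If the pain fails to be relieved during the intervention, the project team must be informed in time". The action attached to that trigger is that "relevant drugs must be given if necessary". It then escalates: "if the symptoms cannot be relieved, comprehensive treatment should be given immediately".
- **Dropout Criteria:** the section covers participants who could not complete the trial. Criterion 1 reads "patients are not treated by the regulations, and the curative effect cannot be judged"; criterion 2 is "incomplete data that affect the judgment of efficacy or safety".
- **Comprehensive Suspension Criteria:** one ground is that "participants experience severe complications or disease deterioration during the study period", a further event related to outcome.

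The Blinding section says that neither patients nor therapists are blinded. Under Sample Size Calculation, 30 per group is raised to 38 for 20% dropout.

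**The concern.** Staff who follow the quality-control section and give a drug breach the Interventions section, and nothing in the article tells them which instruction prevails. The trigger is unrelieved pain, so the patients affected are those in whom the assigned treatment is failing.

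Once a drug has been given, staff may conclude that the effect of the assigned treatment can no longer be judged. That conclusion opens dropout criterion 1. Whether the patient still contributes day-14 data would then rest on a judgment made after randomisation, linked to outcome, in a trial where patient and therapist know the arm. Requests for drugs, offers of drugs and the dropout label could all differ between arms.

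Two things are at stake. If such patients are lost, failures disappear from the comparison. If they stay and nobody records the drug, part of their day-14 pain score reflects the drug. The second scan, which carries the primary outcome and falls within 6 hours of the last intervention, could be affected too, in patients who were eligible only if they had taken no painkillers for nearly a month.

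**Working it through.** **Step 1: the text side by side.**

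| Question | Interventions | Quality Control of the Research Participants |
|---|---|---|
| Medicines during treatment? | Not allowed, no exception | Other methods banned, but drugs to be given if necessary when pain is unrelieved |
| Further treatment if symptoms persist? | Acupuncture, physiotherapy and the like not allowed | Comprehensive treatment, immediately |

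The conditional wording limits when drugs are given. It does not create an exception in the Interventions section.

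**Step 2: the route to dropout.** Criterion 1 has two limbs: treatment not according to the rules, and an effect that cannot be judged. A drug-treated patient meets the first limb if the Interventions section governs. The second limb is left to staff. Removal is therefore possible but not automatic.

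**Step 3: the protocol's own figures.** The planned difference is 5.68 − 4.28 = 1.40 VAS points, with SDs 1.26 (traction) and 1.16 (Tuina). The dropout step reproduces: 30 / (1 − 0.20) = 37.5, rounded up to 38 per group. The point does not depend on how the 30 was obtained.

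**Step 4: an illustration of direction and size.** The documents give no rate of drug use, so I assume that a patient whose final VAS would exceed a cut-off c counts as a failure, that scores are normal with the protocol's means and SDs, and that c lies between 6 and 7.5. With a = (c − mean)/SD:

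- proportion failing = 1 − Φ(a);
- mean of those left if failures are removed = mean − SD × φ(a)/Φ(a);
- difference if failures stay and a drug lowers their VAS by r = 1.40 − r × (control failing − Tuina failing), with r assumed to be 1 or 2.

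For c = 6, Tuina: a = (6 − 4.28)/1.16 = 1.483, failing 6.9%, mean of those left 4.28 − 1.16 × 0.1329/0.9309 = 4.11. Control: a = (6 − 5.68)/1.26 = 0.254, failing 40.0%, mean of those left 5.68 − 1.26 × 0.3863/0.6002 = 4.87. The difference is about 0.75.

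| c | Tuina failing | Control failing | Difference, failures removed | Difference, kept, r = 1 | Difference, kept, r = 2 |
|---|---|---|---|---|---|
| 7.5 | 0.3% | 7.5% | 1.22 | 1.33 | 1.26 |
| 7 | 1.0% | 14.8% | 1.09 | 1.26 | 1.12 |
| 6.5 | 2.8% | 25.8% | 0.93 | 1.17 | 0.94 |
| 6 | 6.9% | 40.0% | 0.75 | 1.07 | 0.74 |

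In every row the control arm fails more often and the difference falls below 1.40. The VAS is part of a secondary outcome. Nothing in the documents allows the same sum for the fMRI measures.

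**The case against.** The strongest reply is that the quality-control paragraph sets the ban and the drug provision together, which reads as a general rule with a discretionary exception. On that reading a patient given a drug has followed the protocol, and someone who finishes 14 days with scores and a scan has neither failed to complete the trial nor clearly become impossible to judge. This stands in part. It rules out the reading that drugs are compulsory whenever pain persists, and the reading that a drug-treated patient is automatically a dropout. It does not supply the exception missing from the Interventions section, and it leaves the second limb of criterion 1 to discretion.

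A reader might also infer that dropouts' collected data will be discarded. The documents do not say so. The Dropout Criteria define who has dropped out, and the 20% allowance fits data that were simply never obtained. Nor is it a fault that the Statistical Analysis section does not mention these patients, since an analysis plan that is not shown may deal with them. Such a plan could not, however, tell staff which instruction to follow or recover day-14 assessments that were never made.

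Finally, the effect on power may be modest. If the difference fell from 1.40 to 1.10 with pooled SD 1.21 and 30 per group, a two-sided t test would still have power of about 0.93, above the planned 0.85. That holds for modest distortion only; at the lower end of the table it would not.

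**Conclusion.** The conflict is in the text, and the sections must be reconciled. The consequence is conditional: the dropout rule permits, but does not require, data loss that depends on treatment failure and could differ by arm.

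The size cannot be fixed from the documents. Under the assumptions shown, the 1.40-point VAS difference would become 1.22 to 0.75 if failures were removed, or 1.33 to 0.74 if they stayed in with unrecorded drug use. These figures rest on assumed cut-offs and an assumed drug effect of 1 to 2 points.

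It is tempting to infer that the plan favours Tuina. The protocol's own assumptions point the other way: failures would be more common in the control arm, so either mechanism would tend to shrink the difference. If the true failure rates were reversed, or unblinded staff gave drugs more readily in one arm, the direction could change. The point merits correction because the remedy is cheap and a lost day-14 assessment cannot be recovered.

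**What to change.** 1. Reconcile the Interventions section with the section on quality control of participants, so that both give the same instruction. Which clinical rule holds is for the investigators.
2. Reword dropout criterion 1 so that receiving additional treatment, or deviating from the assigned treatment, does not by itself make a patient a dropout. State that all randomised patients are assessed and scanned at day 14 and analysed in the arm to which they were allocated.
3. Record any additional drug or treatment, with type and date, in the case report form, and report the rates by arm. The existing adverse-event record covers increased pain and measures taken, but not pain that merely fails to improve.
4. Add a sensitivity analysis that gives such patients the worst rank for pain and ODI. This fits the planned Mann-Whitney comparison.
5. Do not use an fMRI contrast without these patients' scans as a sensitivity analysis, because it would remove the failures again. If it is shown, label it descriptive.

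The cost is protocol wording, one case-report-form field and a little extra analysis. Recruitment was under way when the article was written (21 patients by July 1, 2024), so additional treatment already given to enrolled patients would have to be recovered from their records.

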### Tuina Intervention Group

The standard Tuina procedure will be based on Tuina therapy described in [21]. The specific therapy will be performed as follows (Figure 3).

The Tuina therapist will guide the patient to lie in the prone position and gently press the bladder meridian on both sides of the patient’s waist and buttocks as well as the posterior lateral side of the affected lower limb for 10 minutes of operation.Thereafter, the Tuina therapist will rhythmically press the acupoints of Shenshu (BL23), Dachangshu (BL25), Huantiao (GB30), Chengfu (BL36), Weizhong (BL40), Chengshan (BL57), and Kunlun (BL60) with their fingers at a frequency of 120 times per minute for 10 minutes of operation.Then, the Tuina therapist will guide the patient to lie on their side by using the waist oblique pull method once on the left and once on the right.Finally, the patient is placed in a supine position, and the lower limb on the affected side is raised. The operation is similar to a straight leg lift test, and this process will be repeated several times.

**Figure 3 figure3:**
[figure not shown]
Operation in the Tuina intervention group.

### TENS With Traction Intervention Group

#### Step 1: TENS

The patient lies in the prone position on the treatment bed. In order to treat the patients, the therapist places 2 electrodes of the TENS therapeutic apparatus (WOND2000F0, SUNJAVA) on the Ashi acupoint on the patient’s back and lower limbs. The therapist then changes the stimulation parameters, setting the frequency to 25 Hz and the pulse width to 280 µs. The therapist chooses the maximum intensity based on the patient’s condition and the level that the patient can tolerate. TENS is performed once a day for 20 minutes, and the treatment will be continued for 14 days.

#### Step 2: Traction

Traction will be performed after 10 minutes of TENS. The patient lies on the spine traction bed (TC-30S, MINATO). Once the therapist assists the patient in putting on the traction strap, they determine the traction amount based on the patient’s weight. Initially, the therapist sets the traction volume at 25% of the patient’s body weight, gradually increasing it by 2 kg/time as the patient’s condition changes until it reaches 40%-50% of the patient’s body weight. The therapist allows the patient to lie down and rest for 5 minutes after each traction session. The patient will receive traction once a day, with a duration of 20 minutes each time. The treatment will last for 14 days.

### Outcome Measurements

We will present the trial results by using both objective and subjective indicators. fMRI will be used for the main measurements, reflecting the changes in the participants’ brain structure and functional changes. Short-Form McGill Pain Questionnaire (SF-MPQ), pressure pain thresholds (PPTs), and the Oswestry disability index (ODI) will indicate the degree of pain and lumbar dysfunction and will be used for secondary outcome measurements.

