**Methods:**

This trial will be conducted between May 2024 and April 2025 in the Rehabilitation Hospital affiliated to Fujian University of Traditional Chinese Medicine. Seventy-six participants with LDH will be enrolled for this trial and randomly assigned to 2 groups: Tuina intervention group and TENS with traction intervention group. Participants in both groups will receive treatment for 14 days. fMRI will be performed for the main pain measurements by assessing the effect of the intervention on brain activity before and after the end of the intervention. Short-Form McGill Pain Questionnaire, pressure pain thresholds, and the Oswestry disability index will be used to reflect the degree of pain and lumbar dysfunction, and the results will be used as secondary outcome measurements.

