### Primary Outcome Measurement

The fMRI examination will be performed in the Imaging Department of the Rehabilitation Hospital affiliated to Fujian University of Traditional Chinese Medicine. The first fMRI scan will be performed 1 day before the start of treatment, and the second fMRI scan will be performed within 6 hours after the last intervention. The fMRI data will be collected by a 3.0 Tesla magnetic resonance scanner (MAGNETOM Prisma 3.0T, Siemens) with 64-channel phase-array head coils. During the acquisition process, participants will be required to close their eyes, relax, stay awake, keep their heads fixed as far as possible, and not perform thinking activities. We will perform fMRI at the beginning and end of the experiment.

To acquire the structural images, we will use the following parameters. The T1-weighted imaging scan parameters are as follows: time of repeat=2200 ms, time of echo=2.48 ms, flip angle=8°, field of view=230 mm×230 mm, matrix=256×256, resolution=0.98×0.98×1 mm^3^, slice number=160, and slice thickness=1.0 mm. The functional images will be acquired using the following parameters: time of repeat=2000 ms, time of echo=30 ms, flip angle=90°, field of view=230 mm, matrix=64×64, resolution=3.6×3.6×3.6 mm^3^, slice number=37, slice thickness=3.6 mm, and scan time=10 minutes for 300 timepoints.

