### fMRI Data Processing

#### ALFF Analysis

The ALFF analysis will be performed using the AFNI (Analysis of Functional NeuroImages) software [27]. The fast Fourier transform transforms the filtered time series to the frequency domain (parameters: taper=0%, fast Fourier transform length=shortest) to obtain the power spectrum. Since the power of a given frequency is proportional to the square of the magnitude of this frequency component in the original time series, the square root is calculated at each frequency of the power spectrum, and the average square root ranges from 0.01 Hz to 0.08 Hz at each voxel. This average square root is considered as the ALFF.

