#### ReHo Analysis

The Kendall coefficient of concordance is used to measure the local synchronization of the time series of its nearest neighbor voxels as 
[figure not shown]

[28], where W is the Kendall coefficient of concordance among given voxels, ranging from 0 to 1; Ri is the sum rank of the ith timepoint; R (n+1) K/2 is the mean of Ri; K is the number of time series within a measured cluster (K=7, 19, and 27; K=27 is used in this study); and n is the number of ranks (here n=60). The Kendall coefficient of concordance program is coded in MATLAB [29]. Thus, an individual ReHo map is generated for each data set.

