#### FC Analysis

Differential brain regions obtained by ALFF or ReHo analysis, regions of interest, and differential brain regions will be selected, and FC will be calculated. An FC plot for each participant will be obtained by DynamicBC using the sliding window method. We will select a window length of 50 times of repeat (time of repeat: 100 seconds) with a window overlap of 98% (step size of 1 time of repeat) to calculate the FC for each participant. The FC plots for each participant will be calculated within each window to generate a series of FC plots. The coefficient of variation of the FC map is calculated to measure the temporal variability of intrinsic brain activity. Finally, the FC variability of all the participants will be transformed into standardized *z* scores to enhance the normality of the data by subtracting the mean of each voxel and dividing by the standard deviation [30].

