### Statistical Analysis

Statistical analysis will be conducted using SPSS 26.0 statistical software. Count data will involve the ratio of the sex and age variables compared between the 2 groups via the *χ*^2^ test of the 4-fold table or the Fisher test. The SF-MPQ scores, PPTs, and ODI scores are the rank data. Therefore, the Mann-Whitney *U* test will be used for the intergroup comparison, and the Wilcoxon symbolic test will be applied for the intragroup comparison. Paired 2-sided *t* test will be used to assess the difference in ALFF and ReHo between the 2 groups. In addition, Pearson correlation coefficients will be used to estimate the connection between the seed region and all of the voxels within the whole brain separately based on the patients. Statistical significance will be set at *P*<.05 (2-sided).

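### The primary outcome is an imaging modality: ALFF and ReHo are tested with equal standing at .05 and the contrast is unclear, so the primary false-positive rate exceeds 5% even with perfect voxel-level correction

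*Protocol article*

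**What the plan says.** Under Outcome Measurements the article states that "fMRI will be used for the main measurements", to show changes in both brain structure and function. The section headed Primary Outcome Measurement gives the scan timing ("The first fMRI scan will be performed 1 day before the start of treatment", with a second scan within 6 hours of the last session) and the scanner parameters. It names no derived variable, brain region or contrast.

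Under fMRI Data Processing, three quantities come from the same functional scans:
- ALFF, a voxelwise average over 0.01 to 0.08 Hz: "This average square root is considered as the ALFF".
- ReHo, a voxelwise concordance coefficient: "Thus, an individual ReHo map is generated for each data set".
- Sliding-window FC variability. Its starting regions are described as "Differential brain regions obtained by ALFF or ReHo analysis", and regions of interest are listed beside them.

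None of the three is called primary, and no order is given. Under Statistical Analysis a paired two-sided t "test will be used to assess the difference in ALFF and ReHo between the 2 groups", and one two-sided threshold of P<.05 covers everything. No between-group test of FC variability is named.

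**The concern.** A primary outcome has to tell the reader which single result, or which family of results under a stated rule, answers the trial's question. Here it names a machine. ALFF measures amplitude and ReHo measures local synchrony, so the two can disagree. If ReHo differs between arms and ALFF does not, or the reverse, the article gives no rule for which result is the trial's answer. Either could be reported as the primary finding at the full .05.

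This is separate from correction over voxels. Perfect whole-brain control inside each map still leaves two full-alpha chances.

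The contrast adds a second gap. A paired test suits a before-after comparison within one arm, whereas the sentence describes a difference between two independently randomised groups. On one reading the test does not fit the comparison. On the other, the primary analysis is a within-arm change, which does not answer the comparative objective.

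**Working it through.** **Inputs**
- Significance level: .05, two-sided (Statistical Analysis).
- Maps tested with equal standing: two, ALFF and ReHo (Statistical Analysis).
- Possible third map: FC variability (FC Analysis).
- Correlation between the map-level tests: not in the document, so an assumed range is shown.
- Voxel-level control: each map is assumed to hold .05 exactly over its voxels. The article does not state this. Its Sample Size Calculation mentions multiple-comparison correction only when describing a cited power study. The assumption favours the plan.

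**The plan's own figure.** The article states no family-wise error rate. Its only error figure is the blanket .05, which is what a single named primary contrast would give.

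**Independent maps.** The chance of at least one false positive among k tests is 1 − (1 − .05)^k.
- k = 2: 1 − .95² = .0975.
- k = 3: 1 − .95³ = .1426.

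**Correlated maps.** For k equicorrelated two-sided normal tests with correlation ρ and c = 1.96, the rate is 1 − ∫ φ(u) [Φ((c − √ρ·u)/√(1−ρ)) − Φ((−c − √ρ·u)/√(1−ρ))]^k du. Numerical integration gives:

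| Assumed ρ | ALFF and ReHo (k = 2) | With FC as a third parallel primary (k = 3) |
|---|---|---|
| 0 | 9.75% | 14.3% |
| 0.3 | 9.5% | 13.6% |
| 0.5 | 9.1% | 12.5% |
| 0.8 | 7.8% | 9.8% |
| 0.9 | 7.0% | 8.4% |
| 0.95 | 6.5% | 7.3% |

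**Which column applies.** Where FC seeds come from regions already found on ALFF or ReHo, FC is run only after a first positive. Under a global null it then adds no new first false positive, and k = 2 applies. FC becomes a separate chance only if it is started from the regions of interest that FC Analysis lists without defining, and is then given a group test that Statistical Analysis does not name.

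**After the fix**
- One named primary at .05: 5.0%.
- Two alternative primaries at .025 each: 1 − .975² = 4.94% if independent, and at most 5% under any correlation. Holm across the two is also bounded by 5%.

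**The case against.** The strongest reply is that this is mechanistic imaging work. The Introduction says the trial is designed to explore a potential cerebral mechanism, and alpha allocation and map-level thresholds are commonly left to an analysis plan that is not shown. Part of this stands: an unseen plan might share alpha, and the percentages would then change. But naming the primary variable and contrast is the protocol's task. This article has a primary-outcome section detailed to flip angle and slice count, and a statistics section that fixes the threshold, yet neither says what the primary variable is.

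Four stronger readings are tempting, and the document does not support them.
- A reader might take one figure, such as 9% to 13%, as the trial's error rate. It would rest on a correlation and a whole-brain correction that the article does not state, and its upper end would count FC as a full third test.
- A reader might infer from FC Analysis that a positive ALFF or ReHo map is enough for success. That sentence selects seeds for a follow-on analysis. No section sets a success criterion.
- A reader might see a conflict with the Abstract, which speaks of "assessing the effect of the intervention on brain activity before and after the end of the intervention". Scanning twice and comparing arms are compatible. The ambiguity lies in the paired test under Statistical Analysis.
- A reader might say that FC alone could be reported as the primary result. Without a named group test for FC variability, that is conjecture.

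**Conclusion.** The point holds in limited form. The primary outcome is fixed only as a modality, two maps are tested with equal standing at .05, and the test named does not match the contrast described.

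The resulting chance of a false-positive primary is above 5% at every correlation examined. For ALFF and ReHo it is 9.75% if independent and 7.0% at ρ = 0.9, which is 1.95 to 1.4 times the stated level. These figures rest on an assumed correlation, on assumed exact voxel-level control, and on no alpha-sharing rule existing elsewhere. About 14% is a ceiling that needs independent maps and FC as a third parallel primary. It is not the expected case.

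**What to change.** In Outcome Measurements, Primary Outcome Measurement and Statistical Analysis:
- Define the primary contrast as the between-arm difference in pre-to-post change, and replace the paired test with one suited to two independent groups.
- Before any unblinded analysis, choose one of two options. Either name ALFF or ReHo as the sole primary at whole-brain corrected two-sided .05, or keep both as alternative primaries at .025 each or with Holm. The term co-primary should be avoided here, because it usually means that both must succeed, which needs no split.
- Label FC variability and within-arm before-after maps exploratory.

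No new scans or patients are needed. The article reports that no data analysis had been performed and that statisticians stay blinded, so the choice can still be made without knowledge of results. There are costs. It is a dated amendment to an approved and registered trial, made after enrolment began (21 patients' data collected by July 1, 2024). The per-map threshold is slightly stricter if both maps are kept; because the sample size was built on the visual analog scale, the power lost at .025 per map has not been assessed. FC, or the map not chosen, can no longer be reported as primary.
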